## Abstract

**Background:**

Incomplete adherence to antiretroviral therapy (ART) is one of the factors that contribute to HIV drug resistance, and it is a major problem for the public health system in controlling the HIV pandemic. There is emerging evidence that SMS can play an important role in health care delivery among patients with HIV on ART, especially in resource-limited settings.

**Objective:**

This paper aims to assess the impact of two-way and one-way SMS text messaging on adherence to HIV treatment. We hypothesized that sending weekly text messages through the one-way and two-way SMS text messaging approach will improve adherence to ART among patients with HIV and improve associated clinical outcomes (quality of life).

**Methods:**

A randomized controlled trial is being carried out among participants with HIV who have been on ART for at least one month from an accredited treatment center, namely the Buea Regional Hospital and Kumba District Hospital of South West Region, Cameroon. Participants with HIV, both male and female, aged 21 years and older make up a sample size of 207. The interventions involved the use of mobile phone text messages. Before commencing the intervention, a focus group discussion was carried out among the participants to understand their perception about the use of SMS-based interventions to improve adherence. A total of 246 participants were randomized to receive either a one-way text message (SMS sent to a recipient without recipient sending a reply) or two-way text message (SMS sent to a recipient and recipient sends a reply) or the control (no SMS, only standard care). Data on adherence and quality of life were collected at baseline and after 6 months and will be analyzed using SPSS version 21, while qualitative data will be analyzed using Atlas.ti 7.5.

**Results:**

Data collection began in September 2019 with focus group discussions and baseline data collection. After 1 month of baseline data collection, the intervention began in October 2019, and postintervention data were collected after 6 months (March 2020). At the end of the study, we will be able to understand the perception of patients toward SMS text messaging–based interventions and also assess the impact of one-way and two-way SMS text messages on treatment adherence among patients with HIV and on associated clinical outcomes (quality of life).

**Conclusions:**

The impact of SMS text messaging varies across different settings. The results from this study will determine the perception of patients toward an SMS text messaging–based intervention and its impact on adherence to ART.

**International Registered Report Identifier (IRRID):**

DERR1-10.2196/16127

## Introduction

Medication adherence is defined by the World Health Organization as the degree to which a person's behavior corresponds with the agreed recommendations from a health care provider or as the extent to which the patient's history of therapeutic drug taking coincides with the prescribed treatment. The Joint United Nations Programme for HIV and AIDS (UNAIDS) has deﬁned new ambitious targets that call for 90% of people living with HIV to know their status, 90% of those diagnosed to receive antiretroviral therapy (ART), and 90% of those on treatment to achieve an undetectable viral load. This is known as the 90-90-90 target [1]. In 2018, 37.9 million people were living with HIV worldwide [2]. Scale-up of antiretroviral therapy is on a fast-track trajectory that has surpassed expectations. The global coverage of antiretroviral therapy reached 46% (43%-50%) at the end of 2015 [1]. In sub-Saharan Africa, where the majority of people receiving antiretroviral therapy live, timely access to HIV diagnosis and linkage to care remain the main challenges to achieving the 90-90-90 objective. In 2018 in Cameroon, 74% of people living with HIV knew their status, and only 52% of people living with HIV were on treatment [2].

Incomplete adherence to antiretroviral therapy is one of the factors that contribute to HIV drug resistance, HIV disease progression, and death [3,4]. Most patients do not adhere to ART due to the long duration of HIV treatment (lifelong therapy) and associated side effects [5]. Diverse strategies have been tested and implemented to help improve adherence to ART.

There is emerging evidence that mobile phones can play an important role in health care delivery, especially in resource-limited settings [6]. The use of phones to promote adherence has grown as phone ownership rates continue to rise in sub-Saharan Africa and elsewhere [7,8]. SMS text messaging is a particularly useful application that can be used to collect or share information and to enhance communication between health care personnel and patients in a low-cost manner [9]. With regard to patient management, mobile phone text messages have been demonstrated to induce positive behavior changes in domains such as smoking cessation, physical activity, and self-management of high blood pressure, diabetes, and asthma [10]. Other studies report high levels of satisfaction among participants [11,12]. Considering these studies, it is possible to conclude that SMS is effective in inducing a positive behavior change and providing greater connectedness with a provider.

Some studies have shown the effectiveness of SMS in improving adherence. For example, a recent Cochrane systematic review synthesizing data from 2 trials conducted in Kenya by Lester and colleagues [12] showed that text messaging is efficacious in improving adherence. They tested a two-way SMS intervention in which recipients in the intervention group were required to respond to weekly messages inquiring about their well-being within 48 hours, with those indicating that they did not feel well or not responding at all receiving outreach from clinic staff. They found a 12 percentage point increase in the likelihood of self-reported adherence greater than 95% among HIV-positive adults in 3 clinics, as well as a 9 percentage point increase in rates of viral suppression. The use of SMS text messaging was also shown to be effective by Pop-Eleches and colleagues [13]. They reported a 13 percentage point increase in the likelihood of achieving at least 90% electronically monitored adherence over 48 weeks in the intervention group that received one-way weekly SMS messages. In another study, Hailey and Arscott [14] showed a significant increase in adherence rates (40% to 50% at baseline to 80% after 24 months) among youths living with HIV after sending a text message reminder and receiving a reply over a 24-month period. However, the youths did not send text messages about their drug refills, shortages of their medications, and adverse effects of the medications they were receiving. Due to the fact that this intervention prevented the patients from sending text messages about adverse effects and the state of their well-being, it is possible to question their quality of life and its impact on adherence. Though SMS text messaging can increase adherence rate, poor quality of life can affect adherence if the content of the text does not address issues related to quality of life.

A study carried out in Cameroon reported a contrary view on SMS text messaging improving adherence [15]. In addition, another study carried out by Linnemayr and colleagues [16] also reported the ineffectiveness of SMS text messaging in improving adherence.

However, despite the quality of evidence generated from literature [10-14] on the importance of SMS-based interventions in improving adherence treatment, especially ART, it remains unclear if the efficacies observed in this existing literature translate into effectiveness in different settings. The fact that a text messaging intervention is effective in a particular setting does not signify its effectiveness in other settings. Some text message–based interventions are ineffective because researchers did not understand or take into consideration the conditions under which the SMS text messaging intervention should be implemented and the content of the message. It is also important to find out what aspect of behavior change the text messaging affects and how it can generally cause behavior change. The findings from this study will be used by health care providers to effectively design an SMS text messaging intervention that is applicable to the setting and the target population.

The general objective of this study will be to assess the impact of the interventions (two-way and one-way SMS) on adherence to ART. We hypothesize that sending weekly text messages through the one-way and two-way SMS text messaging approach will improve adherence to ART among patients with HIV and improve associated outcomes (quality of life).

## Methods

### Study Setting and Participants

The participants were selected from accredited treatment centers, namely the Buea Regional Hospital and Kumba District Hospital of South West Region, Cameroon. Participants included adults (male and female) aged 21 years and older who were infected with HIV and visiting the health centers for routine health education and drug refill appointments. The study recruited participants that were on highly active antiretroviral therapy (HAART) for at least 1 month and who had mobile phones and were able to read and send text messages. We excluded pregnant women and patients with drug-resistant HIV prior to the commencement of the study.

### Study Design

A qualitative study design involving the use of focus group discussions (FGDs) was used to assess the perception of patients on the use of SMS text messaging–based intervention. Thereafter, a quantitative study design involving a randomized controlled trial was carried out. The intervention used one-way or two-way SMS text messaging. Adherence and quality of life (QoL) were measured at baseline and at postintervention in control and intervention groups. Adherence in the control group will be compared with the adherence in the intervention groups before and after the intervention. Likewise, the QoL in the control group will be compared with the QoL in the intervention groups before and after the intervention. In addition, the impact of adherence on QoL will be assessed in the control group and intervention groups before and after the intervention.

### Intervention

The interventions involved the use of mobile phone text messages in addition to the standard care provided to the participants. Participants were randomized into either a one-way text message group (text message sent without receiving a reply) or two-way text message group (text message sent to recipients and the recipient replies to the SMS sent). Text messages were sent both in English and in French, and airtime was purchased from the mobile telephone network. In the morning periods, messages were sent 3 times a week (Mondays, Wednesdays, and Fridays between 8 AM and 10 AM) from an established list of phone numbers of the participants during the study period. The control group received only the standard care given at the hospital. The random allocation of participants in the intervention and control group is shown in Figure 1. The intervention used in this study is based on the nudge theory, which is an approach to understanding and changing people's behavior by analyzing, improving, designing, and offering free choices for people so that their decisions are more likely to produce helpful outcomes for those people and society generally. The SMS text messaging acts as a nudge in order to influence a positive behavior change, which is adherence to ART.

**Figure 1 figure1:**
[figure not shown]
Flow diagram on the randomization of participants into the intervention and control groups. HAART: highly active antiretroviral therapy.

### Study Duration

This study will be carried out over a period of 1 year. The intervention phase ran for 6 months after collecting baseline data (preintervention data) on adherence and quality of life.

### Sample Size

The formula by Chan [17] for calculating the sample size for randomized controlled trials was used:

In the above equation, *c* = 7.9 for 80% power and *p*1 and *p*2 are the proportion estimates (60% for the control group and 82% for the intervention group).

n (size per group) = 63.27 **(3)**

It was assumed that 30% of the participants would drop out of the study due to loss to follow-up and mortality. A total of 82 participants were then randomized to each group to allow for the 30% drop out (30% of 63 participants = 19). In order to make up for the 19 that was assumed to be lost to follow-up, we added the 19 participants to the calculated 63 participants, giving a total of 82 participants. Therefore, a minimum of 246 participants were recruited into the study.

The above sample size in each group was distributed with 164 in the intervention group (82 in the two-way SMS group and 82 in the one-way SMS group) and 82 in the control group.

### Evaluation of Intervention

A logbook was used to register all SMS text messages sent and replies received on the designated days of the week. A delivery report function was used to ensure that the messages were delivered to the participants. The sent text and responses received will be evaluated by calculating the proportion of SMS text messages sent and responses received. Example text messages are shown in Textbox 1.

Examples of the text messages that were sent.“Hello. Do remember to take your medication as prescribed. Your health is your wealth.”“You are kindly reminded to take your medication. Your health is our priority.”“Don’t forget to take your medications.”

### Randomization

Using a simple randomization technique, participants were recruited into the intervention and control group. Allocation of the participants into the groups (intervention or control) was concealed during the randomization procedure. This shall be a double-blind controlled trial: data collectors and the statistician shall be blinded to the different group allocations.

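### Simple randomization is stated, yet exactly 82 are reported as randomized to each of three arms: the allocation method or the arm counts are very probably misdescribed

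*Protocol article*

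**What the plan says.** The Randomization section of the protocol article describes the method in one sentence: "Using a simple randomization technique, participants were recruited into the intervention and control group". It adds that allocation was concealed. It mentions no restriction of any kind.

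The Sample Size section derives 63 per group, adds 19 for dropout, and then reports: "A total of 82 participants were then randomized to each group to allow for the 30% drop out". It repeats the split as "164 in the intervention group (82 in the two-way SMS group and 82 in the one-way SMS group) and 82 in the control group". The Methods paragraph of the abstract agrees on the total: "A total of 246 participants were randomized to receive either a one-way text message". The Sample Size section also calls that total a lower limit: "Therefore, a minimum of 246 participants were recruited into the study".

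Participants came from two sites, "Buea Regional Hospital and Kumba District Hospital". For both binary adherence outcomes, Table 1 specifies a chi-square test and lists no hospital term.

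**The concern.** Under simple randomization each participant is assigned independently of all the others, so the arm sizes are themselves random. Three arms that all land exactly on the planned figure are the signature of a restricted scheme, such as blocks or a list with a fixed number of places per arm. They can also mean that a planning target was reported as if it were the count allocated. The article states the unrestricted method and the exactly equal arms as facts, and the two sit badly together.

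At stake is whether a reader can tell how the trial was randomized. Under true simple randomization the next assignment can never be predicted. Under a fixed-size list, late assignments become more predictable as arms fill. The real method is therefore needed to judge the concealment that the article claims. If 82 per arm was only the target, the true denominators are not in the article.

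A smaller, separate matter is that the method as stated does nothing to balance the two hospitals across arms, and the primary test as stated does not account for hospital.

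**Working it through.** **Inputs.** Total 246 and 82 per arm (abstract and Sample Size); three arms allocated 1:1:1 (Sample Size); simple randomization (Randomization); adherence proportions of "60% for the control group and 82% for the intervention group", *c* = 7.9 and 30% dropout (Sample Size); two-sided 0.05 level (Data Management and Statistical Analysis).

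**1. The plan's own figures.** The formula is *n* = *c*[*p*1(1−*p*1) + *p*2(1−*p*2)]/(*p*1−*p*2)². With the inputs it gives 7.9 × (0.24 + 0.1476)/0.0484 = 63.27, as stated. Then 30% of 63 is 19, 63 + 19 = 82, and 3 × 82 = 246. The stated sizes reproduce.

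**2. Chance of exactly equal arms.** Under simple 1:1:1 randomization, P(82/82/82) = 246!/(82!³ × 3²⁴⁶) = 0.00335. That is 0.34%, or about 1 in 300.

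**3. Spread of arm sizes.** The standard deviation of one arm is √(246 × 1/3 × 2/3) = 7.39. Simulated allocations give:

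| Quantity | Result |
|---|---|
| 95% range of one arm | about 68 to 97 |
| Mean size of the smallest arm | 74.4 |
| Gap, largest minus smallest: mean | 15.3 |
| Gap: median (5th to 95th percentile) | 14 (4 to 30) |
| Gap of 2 or less | 2.3% of allocations |

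With 246 people, all three arms can reach at least 82 only if all three equal 82.

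The small probability alone does not settle the matter. With equal allocation, 82/82/82 is the single most likely triple, and every other triple is rarer still. What counts is the contrast: a fixed-size scheme produces this split by design, simple randomization produces it about 1 time in 300, and it coincides with the planning target.

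**4. Effect on power.** This uses a pooled two-sided test of 60% v 82%, control against one SMS arm:

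| | Fixed 82 v 82 | Averaged over simple randomization |
|---|---|---|
| No loss | 88.1% | 87.8% |
| 70% retained (82 × 0.7 = 57.4 per arm) | 74.4% | 74.1% |

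Simple randomization costs 0.3 points in either row. The low values in the second row are present with perfectly equal arms. They come from inflating by 1.30 instead of dividing by 0.70 (63/0.70 = 90), and from the pooled test, which gives 78.4% even at 63 v 63.

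**5. Hospital mix.** The article does not give the split between hospitals, so a share *s* has to be assumed. The standard deviation of the difference in hospital share between two arms of 82 is √(2*s*(1−*s*)/82). This is 7.8 points at *s* = 0.5 and 6.2 points at *s* = 0.2. These figures describe what chance can do under the stated method; they do not show that it happened.

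**The case against.** The best defence is that the two passages can be read together. The Sample Size section derives a target, and 246 is called a minimum, so 82 may be a planned figure written in the wrong tense. The word simple may also be used loosely for drawing from a fixed number of lots per arm, which gives 82/82/82 by design. And 1 in 300 is not impossible. All of this is fair. It rules out saying that one of the two statements must be wrong. It does not remove the need to correct the text, because the first reading means the counts are misreported and the second means the method is misnamed. Condensation does not answer the point either, since the problem is two statements that the article does make.

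Three stronger readings are tempting, and the documents do not support them:

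- **That the power cannot be relied on because of the randomization method.** The cost is 0.3 points. The dropout inflation is a different matter.
- **That the hospitals were unbalanced, or that the comparison is biased.** No figure on hospital mix is given. Unstratified randomization does not bias the comparison, and the unadjusted chi-square test remains valid because chance imbalance is already within its type I error.
- **That allocation was steered towards equal groups.** Nothing in the article suggests this, and it states that allocation was concealed.

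A hospital-adjusted analysis may also stand in a full protocol or analysis plan that is not shown. The hospital recommendation is therefore an improvement to the test fixed in Table 1 and not a charge of omission.

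**Conclusion.** The inconsistency holds. The article pairs simple randomization, with no restriction mentioned, with "82 in the two-way SMS group and 82 in the one-way SMS group" and 82 in control, a split that this method gives about 0.3% of the time (arm standard deviation 7.4, expected gap about 15). It is therefore very probable, though not certain, that either the allocation method or the arm counts are misdescribed. The conclusion assumes equal 1:1:1 probabilities, exactly 246 people allocated, and the strict meaning of simple randomization. It also rests on the judgement that a loosely named restricted scheme, or a target reported as a count, is far more common than a 1-in-300 coincidence.

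This is a fault in describing the procedure. It is not a loss of power or a source of bias. The hospital point is secondary: adjustment would remove chance imbalance in hospital mix from the comparison and may add some precision, by an amount the documents do not allow one to state.

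**What to change.** Reconcile the Randomization and Sample Size sections:

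- If allocation was restricted, name the method (blocks or a fixed-size list) in place of the present label.
- If it was truly simple, replace 82/82/82 with the numbers actually allocated to each arm, and present 82 as the planned size only.
- If it was truly simple and the counts really were 82/82/82, say so expressly.

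Separately, in Table 1, replace the plain chi-square test for the two adherence outcomes with a Cochran-Mantel-Haenszel test stratified by hospital, or with logistic regression including hospital as a covariate. Fix the choice before any unblinded analysis.

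The cost is one or two sentences and one changed table entry. Hospital is already known for each participant, so no new participants or data are needed.

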### Data Collection Tools

A pretested structured questionnaire was used to obtain information from the participants on sociodemographic characteristics, adherence to treatment, quality of life, and past health history. A logbook was used to report on all messages that were sent during the week and the number of replies received, and the research team recorded all defaulters and participants lost to follow-up.

#### Measurement of Adherence

The overall adherence of each participant was measured using 2 scales of self-report, namely the visual analog scale (VAS) [18] and the Center for Adherence Support Evaluation (CASE) Adherence Index [19]. VAS appears to be a simple and easy to use measure of adherence, though there is mixed literature about this. VAS has been shown to have large strength associations with most other measures of adherence. A 100-point VAS will be used, with 0 indicating “absolute nonadherence” and 100 indicating “excellent adherence” in the last 30 days. A VAS score equating to at least 95% will be defined as optimal adherence and VAS scores less than 95% will be considered suboptimal.

The CASE Adherence Index is a simple composite measure of self-reported ART adherence. Based on the results of correlation and principal components analyses, the CASE Adherence Index is developed as a composite (sum) of 3 self-reported measures of adherence. The CASE Adherence Index can be seen in Multimedia Appendix 1.

#### Measurement of Quality of Life

The quality of life was assessed using the abbreviated World Health Organization Quality of Life (WHOQOL-BREF). This is an international, cross-culturally comparable quality of life assessment instrument. It assesses the individual's perceptions in the context of their culture and value systems and their personal goals, standards, and concerns. The WHOQOL-BREF instrument comprises 26 items, which measure the following broad domains: physical health, psychological health, social relationships, and environment [20]. The quality of life among the participants with HIV was assessed using the WHOQOL-HIV BREF. The WHOQOL-HIV BREF is based on the WHOQOL-BREF, the shorter form of the WHOQOL-100. This contains 5 extra items specific to people living with HIV/AIDS and in total contains 31 items [21].

